## Abstract

**Background:**

The shortage of general practitioners (GPs) in Germany, particularly in rural areas, is a pressing issue that requires innovative and sustainable solutions. One promising approach is the integration of trained medical assistants to support GPs by handling specific tasks, thus enhancing the efficiency of healthcare delivery. Delegated home visits can be carried out by healthcare professionals (HPs) with a well-defined range of tasks.

**Methods:**

This quasi-experimental, non-randomised longitudinal observational study runs from January 2023 to June 2025. The study participants are patients cared for by participating GPs, selected based on defined inclusion criteria, who receive regularly delegated home visits. Health-related quality of life (HRQoL) and satisfaction is assessed at three data collection points (t0 as baseline before starting the intervention, t1 after the first testing and data collection phase, and t2 after the second data collection phase). For assessing the HRQoL, we use the Short-Form-Health Survey (SF-12), and satisfaction is being measured using the patient satisfaction questionnaire ZUF-8. These parameters, as well as the continuously collected parameters (kilometers driven, travel and setup time), are analysed statistically (descriptive statistics, paired t test, Wilcoxon test, ANOVA). At t1 and t2, focus group interviews are conducted with the assistants on their satisfaction. They allow to identify the potential for concept improvement by qualitative content analysis.

**Discussion:**

The “VERSORGT am ORT” (VaO, engl. “PROVIDED on SITE”) project aims to optimise healthcare by using scarce resources in a more efficient way, maintaining patient-professional trust, and extending delegation. It seeks to implement care plans with minimal location changes and generate real-world evidence. Due to geographical and policy limitations, the study will have comparatively few participants and will use a repeated measures design instead of a control group to assess patient HRQoL and satisfaction over time. Changes in HRQoL cannot be directly linked to the new care model due to unclear causalities. Mergenthal et al. reported that 59% of GPs in rural areas delegate home visits to healthcare professionals, saving time. The VaO project aims to further relieve GPs, increasing efficiency without compromising care quality.

**Trial registration:**

DRKS00033915 – Registration Date 19/03/2024.

**Supplementary Information:**

The online version contains supplementary material available at 10.1186/s12913-025-12742-5.

## Background

One of the stated objectives of the EU Member States is to ensure access to modern and efficient healthcare for all [1]. However, Germany faces challenges to providing regionally equitable healthcare. Rural areas, in particular, are at risk of reduced medical services, with many patients experiencing dwindling medical resources. As demographic shifts and rising life expectancy lead to an increasing number of older patients with multiple chronic conditions, the availability of medical care continues to decline. This growing demand necessitates innovative approaches to healthcare delivery [2].

Germany ranks in the upper third of the 32 Organisation for Economic Cooperation and Development (OECD) countries in terms of general practitioner density [3]. In 2023, the absolute number of GPs practicing in Germany was 55,127 [4], representing 36% of ll 153,726 SHI-accredited physicians [5]. However, their distribution is uneven, resulting in inadequate primary care in some regions. Demographic change will exacerbate this situation, with 11.9% of themedical workforce aged over 65 by 2022 [6], leading to an anticipated shortfall of 10,851 GP posts that will remain unfilled in 2035 [7]. Overall, there is an urgent need to promote young talent to take over vacant doctor offices, as the age-related retirement of many GPs is being offset by an acute shortage of young talent [8].

A semiannual audit of the Bavarian Association of Statutory Health Insurance Physicians (Kassenärztliche Vereinigung Bayern, KVB) indicated that rural healthcare in Bavaria, particularly in the field of GPs, is at risk in many regions [9]. This is where the innovative VaO care model comes in and analyses the structures of existing delegation concepts in order to organise the care of home-visit patients in a more efficient way. The almost 25,000 inhabitants of our examined example region, the Streutal Valley in Northern Bavaria, are already facing this situation mentioned above. The structure of the eleven regional GPs with an average age of 66.8 years facing an average retirement age in Germany of 64.4 years in 2022 suggests that some of them will retire in the coming years [10, 11]. A study by the University of Trier shows the resulting difficulty: 36% of all human medicine doctors in Germany are GPs [5] but only 12% of the students tend to this subject [12].

Several delegation concepts exist and aim to reduce the workload of GPs, such as different types of specialised care assistants, ‘care assistants in the GP practice’ (VERAH), ‘nonphysician practice assistants’ (NäPA) or ‘physician-supported, community-based, e-health-supported, systemic intervention’ (AGnES)- hereafter referred to as healthcare professionals (HPs). These specially trained HPs can carry out defined activities delegated by GPs, including home visits. This frees up GP time for patient care, especially in rural areas with long distances to and between patients’ homes [13].

The delegation of GPs’ activities is therefore a promising strategy to address care gaps. However, the availability of delegation recipients is also finite. To maximize the efficiency of healthcare services, it is crucial to optimise the organization of service provision. The VaO concept addresses this by relocating home visits to nearby, well-equipped VaO rooms for patients who are physically able to access them. These rooms serve as treatment centers used exclusively by healthcare professionals (HPs) and patients with GP recommendations. Within the VaO care model, the scope of services and the HPs delivering them stay as they are established, medical management remains under GP supervision. Services provided include measuring blood sugar levels, changing dressings, or taking blood samples, as defined by the Agreement on the delegation of medical services to nonmedical staff in outpatient care of contract physicians care in accordance with § 28 Para. 1 S. 3 SGB V by the Association of Statutory Health Insurance Physicians in cooperation with the National Association of Statutory Health Insurance Funds [14].

## Objectives

The overall aim is to (1) implement the VaO concept in a real-world setting in the Streutal Valley in Northern Bavaria and to (2) evaluate its effectiveness by assessing economic efficiency, satisfaction and HRQoL in compared to the usual care provision.

Therefore, the primary objective is to conduct a health economic evaluation of VaO as a minor modification and resource-saving interdisciplinary form of care to mitigate the shortage of GPs in rural areas. The secondary objective is to test its feasibility and integration into the daily routines of patients, HPs and GPs as well as to evaluate the psychosocial effects of the concept. The following hypotheses are being tested to answer the selected research question.

Hypothesis 1: The monetary expenses and savings of the VaO care model lead to economically neutral to positive results for the GPs running the rooms.Hypothesis 2: The VaO care model reduces average working time spent in nonpatient areas (travel and setup time).Hypothesis 3: The VaO concept does not lead to a change in patients’ HRQoL.Hypothesis 4: The VaO concept does not lead to a change in patients’ and HPs satisfaction.

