### Trial design

The study is designed as a non-randomised, single-arm longitudinal observational study with repeated measurement points in the context of health services research. It is conducted from January 2023 to June 2025, spanning a total duration of 30 months and comprising five phases. The first one, the preparatory phase focused on the requirements of implementation. These were assessed by participating GPs and selected according to the following criteria: (1) village where home visits are carried out (2), number of patients receiving home visits, and (3) share suitable for visiting a VaO room. Suitable premises were selected in collaboration with local mayors. A checklist in accordance with the Association of General Practitioners in Germany (VirchowBund) was used to ensure alignment of the facilities [15]. The criteria included, for example, accessibility, sanitary facilities and stable internet connections. The rooms were inspected by HPs and GPs.

In the initial assessment and testing phase, patients’ care in VaO rooms by their known HPs starts. The HPs continuously monitor the patients’ state of health to determine their suitability for care in VaO rooms [16]. The subsequent interim evaluation and concept adjustment phase aims to correct weaknesses, sources of risk and errors from the initial assessment and testing phase by conducting a focus group interview with the participating HPs on their satisfaction with the use of the room. Sources of risk and errors are targeted while adjustments to the VaO concept optimise processes. In the second survey phase, the time and distance parameters of patient care are continuously collected. A final evaluation is carried out at the end of the study to test the hypotheses.

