### Sample size

As the study initially pursues the general proof of concept and has an observational character, it aims to explore complex interactions and the evolution of the use of VaO rooms rather than to quantify specific instances. We see the development of the usage of the VaO rooms, the number of patients receiving care and the given services as indicators of study success. The sample size estimation is conducted using the tool G*Power Version 3.1.9.7 of Heinrich Heine University of Düsseldorf. The calculation is based on an expected effect size of 0.25, an alpha error level of 0.05 and a statistical power of 0.80. Given the repeated measures ANOVA design, the number of groups is set to one with three measurement time points. Additionally, a correlation of 0.5 between repeated measures is assumed, and the nonsphericity correction is set to the default value of one. This results in a required total sample size of 28, with an actual power of 0.81.

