### Statistical methods

#### Statistical methods for primary and secondary outcomes

Table 1 shows the statistical methods used to analyse quantitative data.

**Table 1 Tab1:** Statistical methods used for quantitative data sets

Data	Points in time	Statistical method
SF- 12	t0, t1, t2	Descriptive statistics, paired t test, ANOVA with repeated measures
ZUF- 8	t0, t1, t2	Descriptive statistics, paired t test, ANOVA with repeated measures
Kilometers	continuous	Descriptive statistics, paired t test, Wilcoxon test
Time	continuous	Descriptive statistics, paired t test, Wilcoxon test

The baseline data (t0) on HRQoL and patient satisfaction are analysed using descriptive statistics. To assess the changes that occurred after the first survey and testing phase, data collected at t0 and t1 are compared using paired t-tests or Wilcoxon test as part of an interim analysis. Upon completion of the second survey and testing phase, all data from the three measurement points (t0, t1 and t2) are subjected to a repeated measures ANOVA to compare outcomes across all three time points.

Additionally, the distance travelled and time spent are compared between the VaO scenario and the home visit scenario. Given the conditions shown, paired t tests or Wilcoxon test are used to determine whether there are any discernible differences in the parameters under examination.

The emphasis is on understanding underlying trends, patterns and on gaining real world evidence.

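### Hypothesis 3 and the patient part of Hypothesis 4 assert no change, but the plan contains only difference tests and so no analysis that can support them

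*Protocol article*

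**What the plan says.** The Objectives section introduces four hypotheses as being tested. Two of them assert the absence of an effect: "Hypothesis 3: The VaO concept does not lead to a change in" patients' HRQoL, and "Hypothesis 4: The VaO concept does not lead to a change in patients’ and HPs satisfaction". The Trial design section repeats the intent: "A final evaluation is carried out at the end of the study to test the hypotheses".

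For SF-12 and ZUF-8, Table 1 lists descriptive statistics, the paired t test and repeated measures ANOVA. The text below it assigns the paired t test or Wilcoxon test to t0 versus t1, and at the end all three time points are "subjected to a repeated measures ANOVA to compare outcomes across all three time points".

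The Sample size section powers the same ANOVA: "The calculation is based on an expected effect size of 0.25, an alpha error level of 0.05 and a statistical power of 0.80". It adds that "the number of groups is set to one with three measurement time points" and that "a correlation of 0.5 between repeated measures is assumed", with a nonsphericity correction of one. The result is 28 patients and an actual power of 0.81.

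The article gives no equivalence or non-inferiority margin and no confidence-interval criterion. Satisfaction of the healthcare professionals (HPs) is explored in focus groups at t1 and t2.

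**The concern.** The statements the study wants to uphold are the null hypotheses of its tests. A paired t test, Wilcoxon test or ANOVA can reject no change. If it fails to reject, the cause may be that nothing changed, or that the study was small, noisy or incomplete. Each of the latter makes a non-significant result more likely, and so favours the hypothesis as worded.

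The project offers time savings without loss of quality. Hypothesis 3 and the patient part of Hypothesis 4 are its quantitative patient-level check on the second half of that offer, and the Discussion expects few participants. The mismatch lies in the printed hypotheses, tests and power basis, so it is not a detail left to a fuller document.

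**Working it through.** **Inputs.** From Sample size: f = 0.25, alpha = 0.05, m = 3 time points, one group, correlation rho = 0.5, epsilon = 1, N = 28. Assumed here, because the article gives neither: the time pattern of a true change, and the margins. Changes and margins are in units of the SD at one time point.

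**Step 1: the plan's own figure.** For a within-subject ANOVA, lambda = f² × N × m × epsilon / (1 − rho) = 0.0625 × 28 × 3 / 0.5 = 10.5, with (m − 1) = 2 and (N − 1)(m − 1) = 54 degrees of freedom. The noncentral F gives power 0.812; at N = 27 it is 0.796. So 28 and 0.81 both reproduce. This is the probability of rejecting no change when f = 0.25.

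**Step 2: what f = 0.25 means.** Let d be the change from t0 to t2.
- Linear change (0, d/2, d): f = d/√6, so d = 0.25 × √6 = 0.61 SD.
- Lasting step at t1 (0, d, d): f = d√2/3, so d = 0.25 × 3/√2 = 0.53 SD.

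With t1 lying between t0 and t2, the linear path gives the smallest f for a given d and the step gives the largest, so the two bracket the answer.

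**Step 3: how often a real change is non-significant at N = 28.**

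| True change d | Step: lambda, power | Linear: lambda, power | Non-significant |
|---|---|---|---|
| 0.3 SD | 3.36, 0.339 | 2.52, 0.262 | 66–74% |
| 0.4 SD | 5.97, 0.557 | 4.48, 0.437 | 44–56% |
| 0.5 SD | 9.33, 0.762 | 7.00, 0.629 | 24–37% |

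The paired t test on a single contrast gives 67%, 47% and 28%, inside the same ranges.

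**Step 4: precision.** The SD of a paired change is √(2(1 − rho)) = √(2 × 0.5) = 1 SD. The 95% half-width is t(0.975; 27)/√28 = 2.052/5.292 = 0.39 SD.

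**Step 5: what a test aimed at the claim could deliver.** Per scale, one contrast (t0–t2), N = 28, true change zero:

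| Test | Margin 0.3 SD | Margin 0.5 SD |
|---|---|---|
| Two one-sided tests (TOST), 5% per side | 0.04 | 0.65 |
| Non-inferiority, one-sided 5% | 0.46 | 0.82 |
| Non-inferiority, one-sided 2.5% | 0.33 | 0.72 |

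For 80% power, TOST at 5% per side needs 36 patients at a 0.5 SD margin and 97 at 0.3 SD. The 36 becomes 50 if rho is 0.3 and 22 if rho is 0.7.

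Power falls when several results must all pass. At a 0.5 SD margin, requiring non-inferiority for both t0–t1 and t0–t2 on one scale gives 0.72 (one-sided 5%) or 0.58 (2.5%) by simulation. Requiring it on SF-12 physical, SF-12 mental and ZUF-8 together gives about 0.37–0.48 or 0.20–0.32, for assumed between-scale correlations of 0 to 0.5.

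**The case against.** The strongest reply is that little rests on these hypotheses. HRQoL and satisfaction are secondary outcomes; the primary outcome is travel and setup time. The Sample size section calls the work a proof of concept with observational character, the Statistical methods section stresses trends and patterns, and the Discussion concedes that HRQoL changes cannot be attributed to the care model. In a single-arm study, even a passed equivalence test would not show that VaO leaves HRQoL unchanged.

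This limits the consequences but does not remove the mismatch. The article still says that the hypotheses are tested and quotes an alpha and a power for doing so. The concession is about causal attribution; it does not say that a non-significant test is no evidence of no change.

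A reader might go further and infer that the authors will report a non-significant result as proof of no harm. The documents do not support that. They state no rule equating p > 0.05 with confirmation, and the Discussion bases its expectation of unchanged quality on the care itself being unaltered. What can be said is that the plan gives no criterion by which the hypotheses could be supported.

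A reader might also take all of Hypothesis 4 to be affected. It is not, because the HP part is qualitative. Nor is the phrase expected effect size a separate error: sizing a difference test on a detectable effect is ordinary practice, provided the resulting power is described as power to detect a change.

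**Conclusion.** The point stands for patient HRQoL and patient satisfaction. The hypotheses assert no change, every inferential method listed for SF-12 and ZUF-8 tests for a difference, and the 0.81 is power to reject what the hypotheses assert. The planned analysis can contradict these hypotheses but cannot support them.

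A non-significant result is compatible with real worsening: at 28 patients it would occur in 66–74% of studies with a true change of 0.3 SD and in 24–37% with 0.5 SD. These figures rest on the plan's own rho and epsilon and on complete data from 28 patients. That is the required number, not a stated enrolment, and fewer complete cases would raise the percentages. The margins of 0.3 and 0.5 SD are illustrative.

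**What to change.** 1. For SF-12 physical, SF-12 mental and ZUF-8, report the mean change from t0 to t2 with its confidence interval, and state that a non-significant t test, Wilcoxon test or ANOVA does not confirm Hypothesis 3 or 4.
2. Decide which claim is meant. No relevant change is two-sided and calls for TOST. No relevant worsening is one-sided, calls for non-inferiority, and is a narrower claim than the hypotheses now make. Make either claim only if the interval excludes a margin justified and fixed before analysis. Let t0–t2 be the single deciding contrast and keep t0–t1 descriptive.
3. Say that 0.81 is power to detect a change, and add the power of the chosen test per scale, in the manner of Step 5, noting that it is lower if several scales or contrasts must all pass.
4. Word the conclusion as change over 12 months in patients cared for in VaO rooms, not as an effect of VaO, in line with the Discussion.

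If no margin can be justified, items 1 and 4 and the statement about the 0.81 are still enough to prevent a misreading.

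The cost is rewording two hypotheses, the analysis paragraph and the power sentence, with no new data. The downside is that a margin has to be defended and no change becomes harder to claim: with a margin as tight as 0.3 SD, 28 patients are unlikely to be enough.

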### Trial design

The study is designed as a non-randomised, single-arm longitudinal observational study with repeated measurement points in the context of health services research. It is conducted from January 2023 to June 2025, spanning a total duration of 30 months and comprising five phases. The first one, the preparatory phase focused on the requirements of implementation. These were assessed by participating GPs and selected according to the following criteria: (1) village where home visits are carried out (2), number of patients receiving home visits, and (3) share suitable for visiting a VaO room. Suitable premises were selected in collaboration with local mayors. A checklist in accordance with the Association of General Practitioners in Germany (VirchowBund) was used to ensure alignment of the facilities [15]. The criteria included, for example, accessibility, sanitary facilities and stable internet connections. The rooms were inspected by HPs and GPs.

In the initial assessment and testing phase, patients’ care in VaO rooms by their known HPs starts. The HPs continuously monitor the patients’ state of health to determine their suitability for care in VaO rooms [16]. The subsequent interim evaluation and concept adjustment phase aims to correct weaknesses, sources of risk and errors from the initial assessment and testing phase by conducting a focus group interview with the participating HPs on their satisfaction with the use of the room. Sources of risk and errors are targeted while adjustments to the VaO concept optimise processes. In the second survey phase, the time and distance parameters of patient care are continuously collected. A final evaluation is carried out at the end of the study to test the hypotheses.

### Study setting

The study is being conducted in VaO rooms, which have been specially set up for this purpose. The rooms are furnished and aligned in accordance with criteria of the VirchowBund for medical practices [15]. There are seven VaO rooms located in the villages of Stockheim, Oberstreu, Hendungen, Hausen, Oberwaldbehrungen, Unsleben and Bastheim in the bavarian region Streutal. In the initial assessment and testing phase, those are used and shared by three practices, of which two are joint practices.

### Patient recruitment

Patients are recruited directly by the participating GPs. Patients who meet the following inclusion criteria are contacted directly by their GPs and provided with further information about the study. The final date for patient enrolment is December 31, 2024. Data on travel time, setup time and distance will be collected up to this date. Data on HRQoL and satisfaction will be subjected to analysis for all patients enrolled up to July 31, 2024, in order to be able to map the development over half a year (from t0 to t1).

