### Outcomes

The primary outcomes include time saved in the nonpatient area: travel and setup time. Based on the patients who are cared for and the services that are given in the VaO rooms (VaO scenario), the amount of travel and setup time can be analysed and compared to the time that would have been needed if services were given in the original home visiting route (home visit scenario).

Two secondary outcomes are considered. First, patients’ HRQoL is assessed using the SF- 12 questionnaire which is based on a physical and psychological summated scale. The standardised and validated questionnaire is used because it is known to be simple and quick to administer in the assessment of HRQoL. As a generic measurement instrument for self-reported HRQoL it is particularly suitable for the target group, as it consists of older patients who are asked to make independent statements about their health [17]. The questionnaire is comparatively easy to use as it consists of only 12 items [18]. Second, patient satisfaction is measured using the ZUF- 8 instrument, which is a standardised tool for measuring satisfaction in an inpatient context. It was selected on the basis of its multiple uses in studies and appropriate evaluation of the quality criteria [17, 19]. To examine the changes in HRQoL and patient satisfaction, these parameters are surveyed at three time points during the study, as shown in Fig. 1 (time points t0 as baseline, t1 after six months as midterm, and t2 after 12 months as final examination).

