### Data collection and management

#### Plans for assessment and collection of outcomes

##### Patient satisfaction and HRQoL

The participating patients are administered the SF- 12, a questionnaire frequently used in clinical studies, to assess their HRQoL. Additionally, the ZUF- 8, a questionnaire designed to assess patient satisfaction, is used after being adapted to the context of the “home visit” or “VaO” setting. Both questionnaires are completed at three points in time (t0 before the first VaO room visit of the patient, t1 after six months, t2 after 12 months) during the course of the study to observe and evaluate changes.

In addition, focus group interviews will be conducted with the participating HPs on their satisfaction with VaO concept at survey times t1 and t2. Therefore, we designed an interview guideline which covers important objects like time saving or the changes due to the use of VaO in everyday working life (Appendix A). The interviews are intended to capture the range of opinions of the HPs regarding the innovative VaO concept in an open discussion to validate or question its components. Additionally, potential success factors or barriers to the implementation of the concept will be identified.

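### The 31 July 2024 enrolment cut-off for the questionnaire analysis suits the six-month comparison but not the three-point ANOVA: patients enrolled in July 2024 cannot have a 12-month t2 before the study ends in June 2025

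*Protocol article*

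**What the plan says.** All references are to the protocol article.

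- **Patient recruitment.** Enrolment runs to 31 December 2024, and time and distance data are collected up to that date. For the questionnaires there is an earlier cut-off: "Data on HRQoL and satisfaction will be subjected to analysis for all patients enrolled up to July 31, 2024". The reason given is "in order to be able to map the development over half a year (from t0 to t1").
- **Patient satisfaction and HRQoL.** The schedule per patient is "t0 before the first VaO room visit of the patient, t1 after six months, t2 after 12 months". Outcomes gives the same intervals ("t1 after six months as midterm, and t2 after 12 months as final examination"), and the Discussion repeats six and twelve months.
- **Trial design.** "It is conducted from January 2023 to June 2025, spanning a total duration of 30 months". The same section places the final evaluation, in which the hypotheses are tested, at the end of the study.
- **Statistical methods for primary and secondary outcomes.** t0 and t1 are compared by paired t test or Wilcoxon test as an interim analysis. Afterwards "all data from the three measurement points (t0, t1 and t2) are subjected to a repeated measures ANOVA". No other enrolment cut-off is given for this second analysis.
- **Sample size.** 28 patients, for one group measured at three time points, with actual power 0.81.

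**The concern.** The article fixes four things: the enrolment cut-off, the t2 interval, the study end and the three-point method. They do not fit together. The cut-off works for a six-month follow-up, but the final test of Hypothesis 3 and of the patient part of Hypothesis 4 needs twelve months. The last patients admitted to the questionnaire analysis reach t2 only after the study is over.

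These patients would lack t2 because of the calendar, however well they complied. A classical repeated measures ANOVA uses only patients with all three values, so it would also discard their t0 and t1. The number analysed at three points would then be smaller than the number enrolled by the cut-off.

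The margin is thin. The plan's 28 is the smallest number that reaches power 0.80, and the Discussion expects few participants. Hypotheses 3 and 4 predict no change, so lost power makes a non-significant result more likely, and such a result could be read as support.

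**Working it through.** **Inputs**

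| Input | Value | Section |
|---|---|---|
| Start of recruitment | 22 May 2023 | Trial status |
| Questionnaire cut-off | 31 July 2024 | Patient recruitment |
| t1, t2 | 6 and 12 months | Outcomes; Patient satisfaction and HRQoL; Discussion |
| Study end | June 2025, so 30 June 2025 at the latest | Abstract (Methods); Trial design |
| Effect size f, alpha, correlation, nonsphericity correction | 0.25, 0.05, 0.5, 1 | Sample size |
| Measurements, N, power | 3, 28, 0.81 | Sample size |

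**Step 1. Reproduce the plan's sample size.** For one group and m = 3 measurements, the noncentrality is λ = f² × N × m / (1 − ρ), with m − 1 and (N − 1)(m − 1) degrees of freedom.

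- N = 28: λ = 0.0625 × 28 × 3 / 0.5 = 10.5, df 2 and 54, power 0.812.
- N = 27: λ = 10.125, df 2 and 52, power 0.796.

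So 28 is the smallest N with power of at least 0.80, and the stated 0.81 is reproduced.

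**Step 2. Dates for the last patients admitted.** Taking t0 at enrolment, the favourable case:

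- Enrolled 31 July 2024: t1 = 31 January 2025, inside the study. t2 = 31 July 2025, 31 days after 30 June 2025.
- Enrolled 1 July 2024: t2 = 1 July 2025, one day after.
- Enrolled 30 June 2024: t2 = 30 June 2025, the last possible day.

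**Step 3. Share of the enrolment window.** From 22 May 2023 to 31 July 2024, both days counted, is 437 days. Up to 30 June 2024 it is 406 days. Days without a possible t2: 437 − 406 = 31, and 31/437 = 7.1%.

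**Step 4. Illustration of the effect on power.** Two assumptions that the document does not make: 28 patients are enrolled by 31 July 2024, and they enrol evenly.

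- Patients who can have t2: 28 × 406/437 = 26.0.
- N = 26: λ = 0.0625 × 26 × 3 / 0.5 = 9.75, df 2 and 50, power 0.779.
- To have 28 who can reach t2: 28 × 437/406 = 30.1, so 31 enrolled.

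**Step 5. Sensitivity to the closing date.** The document gives no last questionnaire date. If t2 had to be in by 1 June 2025 (a further assumption), the affected days would be 60 of 437 (13.7%). Of 28 patients, 24 would remain, with power 0.74.

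**Direction of the remaining uncertainty.** Two features push the limit earlier than 30 June 2024. The final evaluation lies inside the 30 months, and t0 is tied to the first VaO room visit, which may come after enrolment. So 7% is a minimum for the share of the window affected.

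**The case against.** The best defence is that the article says what its cut-off is for. It names the half-year from t0 to t1, and the statistical section has a separate paired comparison of exactly those two points. July 2024 enrollees fit it, with t1 by 31 January 2025. This stands. A reader might infer that the questionnaire set cannot be analysed by the planned methods at all, but the paired comparison is a planned method and can use it.

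Second, no sentence says that the ANOVA set is everyone enrolled by 31 July 2024. The text speaks of all data from the three points, and analysis sets and missing-data rules are often left to an analysis plan. This stands in part. The absence of a missing-data rule is not the point. The article states a single questionnaire cut-off, the 12-month interval, the study end and the three-point method, and these conflict as written. It already separates the cut-off for time and distance data from that for questionnaires, but not the two questionnaire analyses.

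Third, the Abstract ties t1 and t2 to study phases, which could allow an earlier t2. But three later sections say 12 months, and a phase-based t2 would give late enrollees a shorter follow-up. A tolerance of a few weeks around t2 could also rescue some July enrollees, but the article states none.

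Fourth, HRQoL and patient satisfaction are secondary outcomes in a proof-of-concept study, and the primary time outcome is untouched. This stands and limits the weight of the point.

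**Conclusion.** The point holds for the three-point ANOVA only. With t2 at 12 months and the study ending in June 2025, patients enrolled on 1 to 31 July 2024 cannot have t2 within the study, although the stated cut-off admits them to the questionnaire analysis. This follows from the article's own dates.

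The certain size is 31 of 437 enrolment days (7%). The fall from 28 to about 26 patients, and in power from 0.81 to about 0.78, is an illustration that rests on even enrolment and on exactly 28 patients by the cut-off.

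Two stronger readings are tempting and not supported.

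- A reader might infer a much larger loss by supposing that questionnaires close well before June 2025. Closing on 31 March 2025, for example, would affect 122 of 437 days (28%) and leave 20 of 28 patients, with power 0.65. The documents give no such date.
- A reader might infer that the sample size is wrong. It is not: 28 is correct for a three-point ANOVA, and nothing says that patients without t2 count towards it. What is missing is the link between that 28 and the patients who can reach t2.

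**What to change.** 1. In Patient recruitment, keep 31 July 2024 for the t0 to t1 comparison only.
2. State the last date on which t2 questionnaires are accepted. Define the three-point set as patients whose t0 plus 12 months falls on or before it. That means t0 no later than 30 June 2024, and earlier if time is reserved for the final evaluation.
3. In Sample size, count the 28 within that set, or restate the power for the number who can reach t2.
4. Analyse the three time points with a mixed model for repeated measures, with time as a categorical factor. Patients who enrolled too late for t2 then still contribute t0 and t1. This is reasonable because their t2 is missing by enrolment date, provided that late enrollees do not differ systematically in their course over time.

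Cost: minor rewording in three sections, slightly more analysis work, and possibly a slightly lower stated power. If the 28 are to be kept among patients who can reach t2, more than 28 must enrol by 31 July 2024 (about 31 under the even-enrolment assumption). If that is not feasible, restating the power is the honest alternative.
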